## Discussion

All statistical tests will be performed two-sided with a level of significance of 5%. The patients will be analyzed as treated. The principle analysis will be on evaluable patients and a supportive intent-to-treat analysis will be performed. Patients will be stratified according to severity of their condition (ASA ≤ 2 vs. ASA > 2); the principle analysis will be stratified, but a non-stratified analysis will also be performed

The groups will be tested for equivalence of distribution of age, sex and body mass index. The analysis will be conducted using analysis of variance with the factors study group and severity of disease, stratified by the Cochran-Mantel-Haenszel test.

95% confidence intervals (CI) for the difference of morbidity rates will be calculated. If and only if this CI lies between -10% and +10% the two procedures will be considered equivalent. The calculation of the 95% CI will be stratified by severity (ASA ≤ 2 vs. ASA > 2). A Breslow-Day test will be performed to check for homogeneity between these two strata.

Amongst the secondary variables, the mean morbidity score in the two groups stratified by severity of disease will be compared using the Wilcoxon rank-sum test. Where appropriate, descriptive statistics will also be performed for all other variables.

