### Immediate surgery versus conservative procedure with subsequent elective surgery

The approach taken is often decided by whether the patient first sees a gastroenterologist, who favors conservative initial antibiotic therapy with later elective surgery, or a surgeon, who favors immediate surgery.

It is still unclear which approach is better in medical and health economic terms. The infection may not respond to conservative treatment on one hand, on the other hand surgical intervention while the disease is acute may increase complications, and conversion to open surgery may be necessary. It is unclear whether it is better to conduct early cholecystectomy, thereby avoiding the risk of recurrent cholecystitis or pancreatitis.

A meta-analysis by Papi et al. (2003) including 12 prospective randomized trials showed no significant difference for morbidity and mortality between immediate surgical intervention (laparoscopic or open) and elective surgery after the acute inflammation had subsided [13]. The numbers of patients and rates of complications were too low to enable any conclusions to be drawn. Also, their definition of "immediate" was between 1 and 7 days after disease onset, while the modern standard favors laparoscopic surgery within 24 hours of onset [14,15].

All studies in the meta-analysis had been performed between 1970 and 2000, and Papi concluded that new studies in an adequate number of patients to show statistical significance should be performed [13]. Two subsequent prospective randomized trials concerning the appropriate timing for surgery also failed to lead to conclusive results, except for a slightly shorter hospital stay in patients treated with immediate surgery [16,17].

In many centers early cholecystectomy is well established although the evidence is not yet conclusive. To our knowledge there has never been a study in which both specialties – gastroenterology and surgery – are equally involved.

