### Number of patients needed

The primary aim of the study is to compare morbidity in the two groups 75 days after enrolment. A difference in morbidity of less than 10% is defined as equivalent. The null-hypothesis is /ρ_M1 _- ρ_M2 _/> 0.1, where ρ_Mi _is the morbidity rate of treatment group i. Complications are expected in 16% of patients in each group; each group therefore needs to enroll 273 patients to permit verification of the null-hypothesis with an α-error of 0.05 and a β-error at 0.15, yielding a power of 90%. Assuming a validity rate of 85%, 322 patients are required per group, resulting in a total patient sample of 644.

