## Primary and secondary endpoints

### Primary endpoints

Primary endpoint is morbidity at the test-of-cure (TOC) visit (75 days after trial inclusion) in the tested population valid for efficacy.

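### The equivalence decision rests on an as-treated, evaluable-patient analysis in which group membership can depend on the outcome, and intent-to-treat has no part in it

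*Protocol article*

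**What the plan says.** Three statements in the protocol article fix the primary analysis.

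- **Grouping and analysis set** (Discussion): "The patients will be analyzed as treated. The principle analysis will be on evaluable patients and a supportive intent-to-treat analysis will be performed".
- **Endpoint population** (Primary endpoints), in agreement with this: the endpoint is assessed "in the tested population valid for efficacy".
- **Decision rule** (Discussion): "If and only if this CI lies between -10% and +10% the two procedures will be considered equivalent". The rule names no analysis set and does not ask for the ITT result to agree.

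The treatment sections give each arm a window for surgery: within 24 hours of admission for immediate surgery, and Days 7 to 45 for the conservative arm. The Background foresees failure of the second strategy: "The infection may not respond to conservative treatment on one hand". Secondary endpoint 4 records antibiotic changes for non-response. The article does not say where a conservative-arm patient operated on before Day 7 is counted.

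**The concern.** The question is which of two strategies, as assigned, gives less morbidity by Day 75. Early surgery after failed antibiotics is one of the ways in which the delayed strategy can turn out, so its complications belong to that strategy.

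Under as-treated grouping such a patient may be counted with surgery. Surgery between 24 hours and Day 7 fits neither arm's window, so the patient may instead fall out of the evaluable set. Failure of antibiotics is plausibly linked to items on the morbidity score in Table 2, such as persistent fever, raised infection markers, abscess and peritonitis. Group membership can therefore depend on the outcome. Surgery-arm patients who miss the 24-hour window raise the same problem. Because the study is unblinded, departures from assignment can also follow clinician preference.

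At stake is the primary conclusion: equivalence could be declared when the arms differ by the margin or more as randomised. The one analysis that keeps the randomised comparison could contradict that conclusion without changing it.

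**Working it through.** **The plan's own figures.** The section on patient numbers gives 16% morbidity in each group, a 10-point margin, 273 evaluable per arm and 85% validity. 273 / 0.85 = 321.2, rounded up to 322 per arm and 644 in total, as stated. The 273 is nearly reproduced (276) by two one-sided tests at 0.05 each, with β = 0.15 split in two and a continuity correction:

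n = 2(0.16)(0.84)(1.645 + 1.440)² / 0.10² = 255.7, or 275.4 after correction.

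The checks below use the stated decision rule, a 95% confidence interval inside ±10 points.

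**Probability of declaring equivalence** (normal approximation, unpooled SE, d = conservative minus surgery):

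P = Φ((0.10 − d)/SE − 1.96) − Φ((−0.10 − d)/SE + 1.96)

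**Benchmark.** True rates as randomised are 16% (surgery) and 26% (conservative), with 273 per arm. Then d = 0.10, SE = 0.0346 and P = 2.5%, the nominal false-equivalence rate.

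**Assumptions.** A fraction f of the conservative arm fails and is operated on early, with morbidity q among those patients. The documents give neither f nor q, so a range is shown. No surgery-arm departures are modelled.

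- Conservative rate once failures leave: r = (0.26 − fq)/(1 − f), on 273(1 − f) patients.
- Failures excluded: compare r with 0.16 on 273.
- Failures counted under surgery: compare r with s = (0.16 + fq)/(1 + f), on 273(1 + f).

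For f = 10%, q = 60%:

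- r = (0.26 − 0.06)/0.90 = 22.2% and s = (0.16 + 0.06)/1.10 = 20.0%.
- Excluded: d = 0.0622, SE = 0.0346, P = 19.0%.
- As treated: d = 0.0222, SE = 0.0352, P = 53.5%.

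| f, q | r | d, excluded | False equivalence | s | d, as treated | False equivalence |
|---|---|---|---|---|---|---|
| 5%, 60% | 24.2% | 8.2 points | 7.4% | 18.1% | 6.1 points | 19.4% |
| 15%, 40% | 23.5% | 7.5 points | 10.1% | 19.1% | 4.4 points | 33.1% |
| 10%, 60% | 22.2% | 6.2 points | 19.0% | 20.0% | 2.2 points | 53.5% |

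**Overshoot.** At f = 20%, q = 80%, as-treated grouping gives r = 12.5% and s = 26.7%. The apparent difference is −14.2 points when the true one is +10. Equivalence is then rarely declared, but the sign is wrong.

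**The case against.** Several objections stand and limit the point.

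- **The evaluable set.** A reader might infer that making evaluable patients principal is itself an error. It is not: such a set is a legitimate companion analysis in an equivalence trial, and ITT will be reported. The faults are the as-treated grouping and the lack of any requirement that ITT agree.
- **The 15% non-valid patients.** A reader might take this allowance as evidence that treatment failures will be dropped. The article gives no reason for the 15%; missed visits, withdrawal or ineligibility could explain it. The definition of evaluable may sit in the full protocol. That failures drop out is an inference from the surgery windows.
- **Surgery outside the window.** It is tempting to say that any conservative-arm operation outside Days 7 to 45 counts as immediate surgery. An operation after Day 45 cannot. One between 24 hours and Day 7 fits neither arm, so leaving the analysis is likelier than moving to surgery. That makes the excluded column the more relevant one.
- **Direction.** Surgery-arm patients who miss 24 hours could be dropped or regrouped too, possibly with the opposite effect. Bias towards the delayed strategy is likely, not established.
- **A shift in the estimate alone.** With 322 per arm, 16% morbidity otherwise and 15% failing at 40%, the difference moves from +3.6 points as randomised to −3.1 as treated. This might look like proof of false equivalence. It is not, because both values lie inside the margin. The chance of claiming equivalence is 56% under ITT and 62% as treated. The harm appears only when the true difference is at or beyond the margin, as in the table.

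None of this answers the central point. The as-treated grouping and the supportive role of ITT are stated choices, not details left open.

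**Conclusion.** The concern holds in this limited form. The plan's primary grouping does not preserve randomisation, and its equivalence rule gives the as-randomised result no say. In the three tabulated scenarios, the nominal 2.5% false-equivalence rate rises to between 7.4% and 19.0% if failures are excluded, and to between 19.4% and 53.5% if they are counted under surgery.

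These figures rest on assumed failure rates and on morbidity among failures, on a true difference exactly at the margin, and on departures in the conservative arm only. They show what the rule permits; they do not forecast this trial. Because the rule governs the primary conclusion and the correction is a change of wording, it should be made before the analysis.

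**What to change.** 1. Replace the as-treated sentence with a statement that every patient is analysed in the randomised arm.
2. State that, for analysis, early or unplanned surgery after failed conservative therapy stays in the conservative arm and does not by itself make a patient non-evaluable.
3. Declare equivalence only if the stratified 95% confidence interval lies within ±10 points in both the ITT and the evaluable sets.
4. Keep an as-treated analysis as a sensitivity analysis at most.

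**Cost.** The chance of claiming equivalence falls. With no true difference (16% in both arms), ITT on 322 per arm has SE 0.0289 and 86.7% power, against SE 0.0314 and 78.0% for 273 evaluable. ITT is then not the limiting set and the loss from requiring both is modest. The ITT analysis needs no extra patients if Day 75 outcomes are obtained for all.

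The loss is larger if failures are common and truly raise conservative-arm morbidity. With 322 per arm and 15% failing at 40%, the conservative rate is 0.85 × 0.16 + 0.15 × 0.40 = 19.6%. The chance is then 56% under ITT, against 83% with failures excluded. In that case the lower chance reflects a real difference between the strategies, but the sponsor should weigh it when confirming the sample size.

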***ASA Physical Status (PS) Classification System from the American Society of Anesthesiologists***	
***ASA PS Category***	***Preoperative Health Status***

ASA PS 1	Normal healthy patient
ASA PS 2	Patients with mild systemic disease
ASA PS 3	Patients with severe systemic disease
ASA PS 4	Patients with severe systemic disease that is a constant threat to life
ASA PS 5	Moribund patients who are not expected to survive without the operation
ASA PS 6	A declared brain-dead patient who organs are being removed for donor purposes

American Society of Anesthesiologists (ASA) Physical Status (PS) Classification System. Categories to classify the preoperative health status of patients.

• Septic shock

• Perforation or abscess of the gall bladder

• No possibility of laparoscopic surgery

• Additional antibiotics needed for secondary disease

• Intolerance to moxifloxacin or other quinolones

• Pregnancy (also suspected), breast feeding

• Life-expectancy < 48 hours

• End-stage liver disease (Child-Pugh C)

• Psychiatric or severe neurologic disease

• Relevant bradycardia or other symptomatic arrhythmias

• Significant cardiac disease

• Disorder with QT prolongation

• Hypocalcaemia or other electrolyte disorders

• Earlier participation in this trial

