## Study treatment

Day 1 is defined as the day the patient presents to the hospital. He undergoes a physical examination, vital signs are documented, and an abdominal ultrasound investigation is performed to confirm the diagnosis of acute cholecystitis. A blood sample is also taken for standard laboratory diagnosis (including Na, K, INR, Hb, platelets, leukocytes, bilirubin, ALT, AST, gamma-GT, AP, amylase, lipase, urea, creatinin and CRP). All relevant concomitant diseases (e.g. coronary heart disease, diabetes mellitus) indicative for morbidity and mortality are recorded [28].

The patient is informed about the trial and is given the opportunity to participate. After the patient has given his informed consent, he is randomized, and all baseline findings, date of birth, age, sex, medical history, height and weight are documented in the CRF.

All patients are examined daily while in the hospital. The laboratory investigations are repeated on Day 3. Samples are taken for microbiological cultures, if necessary. At Day 75 (test-of-cure visit), all diagnostic procedures and treatments between Day 1 and Day 75 are documented. The laboratory determinations and physical examination are repeated, and vital signs are measured. Morbidity is documented according to Table 2.

**Table 2 T2:** Morbidity Score

Persistent abdominal pain > 72 h	1	Pain treated by morphine or derivatives > 72 h
Persistent fever > 72 h	1	Rectal temperature > 38.5°C at least twice
Persistently raised signs of infection > 72 h	1	Persistently elevated CRP or leukocytosis
Wound-healing disorder	2	Any problem leading to re-opening of the wound with subsequent open wound treatment
Thrombosis	3	New onset of leg or pelvic thrombosis
Bleeding	3	Need for more than two bags of packed red cells during or after surgery
Cholangitis	3	New increase in AP, GGT (>2× ULN), bilirubin (>1× ULN) plus leukocytosis (> 12 × 10^3^/μl) or increase in CRP (> 5× ULN)
Icterus	3	New increase in bilirubin, AP and GGT (>2× ULN)
Bile leakage	3	Persistent leakage shown by CT, MRI or ERCP
Abscess	3	Shown by CT, MRI or ultrasound
Pneumonia	3	Shown by X-ray plus drop in arterial pO_2 _plus clinical signs of pneumonia plus leukocytosis plus increased CRP
Embolic lung disease	4	Increased PA pressure (echocardiogram), TNT/TNI, D-dimers
Peritonitis	4	New occurrence of peritonitis
Pancreatitis	4	Increased pancreatic enzymes (> 3× ULN) plus new increase in CRP (> 5× ULN) plus positive clinical signs

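### The equivalence interval adjusts only for two-level ASA class; prespecifying Day-1 age, CRP, leukocytes and temperature as covariates would be a cheap gain in precision of unknown size

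*Protocol article*

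**What the plan says.** The statistical paragraphs in the Discussion section make a 95% confidence interval for the difference in morbidity rates the sole basis for declaring equivalence, with limits of ±10 percentage points. On adjustment they state: "The calculation of the 95% CI will be stratified by severity (ASA ≤ 2 vs. ASA > 2"). A Breslow-Day test checks homogeneity across the two strata, and a non-stratified analysis is added in support. The other model named there has only study group and severity as factors.

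Age appears once, in a comparison of the arms at baseline: "The groups will be tested for equivalence of distribution of age, sex and body mass index". It does not enter the interval.

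The note to Table 1 describes ASA as "Categories to classify the preoperative health status of patients". The exclusion criteria remove classes IV and V, so the stratification compares classes 1-2 with class 3.

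The Study treatment section has vital signs, leukocytes, CRP and other laboratory values taken on Day 1, before consent and randomisation, and records age with the baseline findings. Rectal temperature and leukocytosis are also entry signs. Table 2 scores fever lasting beyond 72 hours and raised infection markers beyond 72 hours, the latter defined as "Persistently elevated CRP or leukocytosis".

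**The concern.** In an equivalence trial decided by whether an interval fits inside fixed limits, the width of that interval governs the chance of success. Baseline variables that predict the outcome narrow it and also correct for chance imbalance in those variables. The plan uses one such variable, ASA, and calls it severity, although its own table defines it as general health status. No measure of how inflamed or septic the patient is at presentation enters the primary comparison, although several are already in the case report form. Testing the arms for similarity in age, sex and body mass index does not narrow the interval.

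At stake is precision that could be had without new patients or new measurements, in a design with little power to spare under its own decision rule.

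**Working it through.** **Inputs from the section on number of patients needed**
- Margin 10 points: "A difference in morbidity of less than 10% is defined as equivalent".
- Rate 16% per arm: "Complications are expected in 16% of patients in each group".
- Evaluable patients: "each group therefore needs to enroll 273 patients".
- Error rates: "with an α-error of 0.05 and a β-error at 0.15, yielding a power of 90" per cent.

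The decision rule (two-sided 95% interval inside ±10 points, that is, two one-sided tests at 0.025) comes from the Discussion section.

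**Assumptions.** R², the share of outcome variance explained by the added covariates beyond ASA, is not in the document; I show 0 to 0.20. ASA itself is taken to explain nothing. The primary yes/no morbidity outcome is taken to count the Table 2 complications.

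**The plan's own sample size.** With n = 2p(1−p)(z₁₋ₐ + z₁₋ᵦ/₂)²/margin²:
- 0.05 per side, β = 0.15: 0.2688 × (1.645 + 1.440)²/0.01 = 256; with continuity correction 276, close to the stated 273.
- 0.025 per side, which the 95% interval implies: 311 per arm for 85% power and 350 for 90%.

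So 273 is approached only with a test at 0.05 per side, not with the 95% interval rule.

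**Current precision at 273 per arm**
- SE = √(2 × 0.16 × 0.84/273) = 0.03138
- Half-width = 1.96 × 0.03138 = 6.15 points
- Power = 2Φ(0.10/0.03138 − 1.96) − 1 = 2Φ(1.227) − 1 = 78.0% (exact binomial calculation: 78.2%)

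**With covariates.** The variance is multiplied by (1 − R²). The last column, 273 × (1 − R²), is the number per arm giving the unadjusted precision.

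| Assumed R² beyond ASA | Half-width (points) | Power | Gain (points) | Equivalent n per arm |
|---|---|---|---|---|
| 0 | 6.15 | 78.0% | – | 273 |
| 0.02 | 6.09 | 79.2% | 1.2 | 268 |
| 0.05 | 5.99 | 81.0% | 3.0 | 259 |
| 0.10 | 5.83 | 83.8% | 5.8 | 246 |
| 0.20 | 5.50 | 89.1% | 11.1 | 218 |

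**What adjustment would have to achieve.** At 273 per arm, 85% power needs R² = 1 − 273/310.6 = 0.12, and 90% needs 1 − 273/349.3 = 0.22.

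**A rough scale for R².** For a logistic model with one normally distributed score at 16% prevalence, R² of 0.02 corresponds to an AUC of about 0.61, 0.047 to about 0.66 and 0.12 to about 0.745. This mapping ignores whatever ASA already explains, so it is for orientation only.

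**Model size.** Expected events are 0.16 × 546 ≈ 87. Six terms (arm, ASA, age, log CRP, leukocytes, temperature) leave 87/6 ≈ 14.5 events per term.

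**The case against.** The strongest reply is that nothing here is wrong. A prespecified, ASA-stratified interval for the risk difference, with a homogeneity check and a non-stratified analysis beside it, is a valid primary analysis. That stands. A reader might infer that the interval is biased or that its coverage fails; the document supports neither.

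A second reply is that the gain is conjecture. This stands in part. No correlation or R² is reported, and at R² of 0.02 the gain is about one point of power. The prognostic argument also has limits. Cholangitis, icterus and pancreatitis in Table 2 each require a new rise in at least one marker, so a high starting value does not simply predict them. Many other items are surgical, thromboembolic or cardiovascular. Entry requires acute signs, and septic shock, perforation and abscess are excluded, which narrows the baseline range.

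Third, the severity label may be called mere wording, because the plan spells out the ASA cut-off beside it. Both arms also go to surgery, so preoperative health is a sensible stratifier, and with only three classes enrolled dichotomising costs little. All of this is fair. It leaves the fact that acute disease severity is not represented in the interval.

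Finally, further adjusted analyses may sit in an analysis plan that is not shown. They may, but the primary interval is fixed in this document, and a supplementary analysis would not change the interval that decides equivalence.

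**Conclusion.** This is an inexpensive improvement to a sound method. Adjusting for four variables already collected would be expected to narrow the primary interval somewhat. Under the plan's inputs and an assumed R² between 0.02 and 0.20, the gain runs from about 1 to 11 points of power, and at R² of 0.05 or below it is at most 3 points. A prognostic link is plausible because persistent fever and persistently raised CRP or leukocytes are themselves scored as morbidity, but the document does not quantify it.

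Two stronger readings should be resisted. One is that the plan forfeits a known amount of power: the amount rests wholly on an assumed R². The other is that adjustment would rescue the design. The 78.0% arises because 273 per arm does not match the 95% interval rule, and a β of 0.15 does not match a power of 90%. Those points need their own correction.

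**What to change.** Keep the risk difference as the estimand and the ±10-point rule unchanged. Prespecify the primary 95% interval from a logistic model with arm, ASA class, age, log CRP, leukocytes and temperature (all Day-1 values), standardised over the analysed patients (g-computation) to give the marginal risk difference, with a robust or delta-method standard error. State a simple rule for missing baseline values, for example single imputation by the overall mean. Keep the ASA-only stratified interval as a sensitivity analysis. Where ASA is called severity of disease, describe it as preoperative health status.

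The cost is analysis wording and a slightly more complex model; no new data or patients are needed. Because the trial is not blinded, the covariates and their functional form must be fixed before outcomes are examined, and with about 87 expected events the list should stay this short.
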